##### Diagnostic criteria

Prediabetes is classified as demonstrating any of the following, according to ADA guidelines [3, 97]:Hemoglobin A1c (HbA_1c_) of 5.7–6.4%Fasting blood glucose of 100–125 mg/dL2-h 75-g Oral Glucose Tolerance Test blood glucose value of 140–199 mg/dL 

##### Source of participants

Study participants will be identified and recruited from community health fairs, diabetes support groups, and directly from clinicians in University of Maryland Medical System outpatient facilities (Baltimore, MD, USA), including the Center for Diabetes and Endocrinology, and Family Medicine Associates. Alliance Integrative Medicine (Cincinnati, OH, USA), and a population of Amish research participants (Lancaster, PA, USA) will serve as additional sources. A member of the research team will screen and include participants via physician referral and/or by verification of laboratory parameters (fasting plasma glucose: 100–125 mg/dL and/or HbA_1c_: 5.7–6.4% and/or postprandial glucose: 140–199 mg/dL), indicating prediabetes status within past 12 weeks, according to ADA guidelines [3]. Male and female participants will be eligible to participate. Based on the racial and ethnic diversity across all sites, a racially and ethnically diverse study population is anticipated.

### Intervention

#### Arrangement for intervention

This study is a multi-site clinical trial, with treatment allocation randomized a priori within each site. This study has received Institutional Review Board (IRB) approval. All research staff have experience with clinical trial recruitment, consenting procedures, and management of clinical and community interventions, and have been trained to uniformly implement all procedures relevant to this study prior to participation. After providing informed consent, participants are instructed on the details of their involvement in the study, including how to use their daily dietary supplement (or placebo) and study diary. Each participant has an in-person baseline assessment, a telephone assessment at 6 weeks, and an in-person assessment at 12 weeks.

#### Polyherbal dietary supplement intervention

GlucoSupreme™ Herbal (Designs for Health®, Suffield, CT, USA) is a polyherbal formula for glycemic control which contains many of the herbs and their standardized extracts that have been previously studied and shown to be potentially efficacious for glycemic control [24, 37–47]. This supplement has been commercially available in the United States since 2009. Each daily serving of four GlucoSupreme™ Herbal capsules includes extracts from: contains cinnamon bark (*Cinnamomum cassia*) 500 mg, banaba leaf (*Lagerstroemia speciosa* standardized to 1% corosolic acid) 200 mg, kudzu root (*Pueraria lobata* standardized to 40% isoflavones) 200 mg, fenugreek seed (*Trigonella foenum-graceum* standardized to contain 60% saponins) 200 mg, and gymnema leaf (*Gymnema sylvestre* standardized to contain 25% gymnemic acid) 200 mg. Additionally, the supplement contains American ginseng root (*Panax quinquefolius* standardized to contain 5% ginsenosides) 200 mg, and berberine HCl derived from bark (*Berberis aristata*) 500 mg. The study treatment is the suggested dosage of this product, and the dosages of active ingredients are comparable or less than those administered in previously conducted clinical studies [20, 22, 37–40, 42, 43, 98–105].

The study sponsor will provide verification data that active study supplement batches contain ingredients as indicated. Other ingredients include cellulose (capsule), microcrystalline cellulose, silicon dioxide, and vegetable stearate. Participants are advised to take each two-capsule serving of GlucoSupreme™ Herbal with food, twice per day (the suggested amount advertised on commercially available bottles), for 12 weeks.

All participants visit their clinic site for two total visits over the 12-week study (i.e., baseline and at 12 weeks). Each visit includes blood sampling. Participants receive their study supplement from the same outpatient physician office, health clinic, or at a home visit. Participants are instructed on how to take the supplement and given appropriate contact information to use for questions or to alert study personnel of any potential adverse events. Each participant receives a bottle labeled only with a group-level identification number unique to randomization group (for which the master study code is accessible only through a locked cabinet by a study coordinator), directions for use, primary research site name, batch number, and IRB protocol number. Participants are asked to record any changes in symptoms and medication or nutritional supplement use in a daily diary using a form reviewed at each study time point.

The intervention and placebo capsules are from the same lot. The placebo utilized in this clinical trial is an inactive dietary supplement composed of cellulose, microcrystalline cellulose, silicon dioxide, and vegetable stearate, and formulated by the manufacturer to be as similar as possible to the active intervention in appearance and other key characteristics. In an attempt to match scent, both active intervention and placebo will have their lid undersides swabbed with a cotton ball containing one drop of cinnamon essential oil (steam-distilled *Cinnamomum zeylanicum* leaf). Packaging for the control group is identical to packaging for the treatment group.

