### Randomization and blinding

Treatment assignment is randomly assigned, in a 1:1 ratio, at each site using a block size of 6. The block randomization sequence schedule is password-controlled by an appointed research team member not involved in the screening or enrolling of participants. The treatment assignments are known to the study coordinator who maintains the allocation master list in a sealed, opaque envelope. Participants, treating clinicians, and outcome assessors are blinded to intervention group status.

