#### Monitoring and inspection

Participant data is entered into an Excel spreadsheet within one week of being collected, and is assessed for integrity and consistency by members of the research team in the following order: the study coordinator, the principal investigator of the study, and statistical sub-investigators for the study. The Standard Protocol Items: Recommendations for Interventional Trials (SPIRIT) Checklist is available in Additional file 1.

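### Bottles carry one code per treatment group, so decoding a single bottle unblinds everyone with that code, and the shared code weakens allocation concealment

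*Protocol article*

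**What the plan says.** - **Label.** The section on the polyherbal supplement intervention states: "Each participant receives a bottle labeled only with a group-level identification number unique to randomization group". The key to these numbers is with the study coordinator: "for which the master study code is accessible only through a locked cabinet by a study coordinator". Bottles are handed out at a physician's office, a health clinic or a home visit.
- **Allocation.** Under Randomization and blinding: "Treatment assignment is randomly assigned, in a 1:1 ratio, at each site using a block size of 6". The sequence itself is "password-controlled by an appointed research team member not involved in the screening or enrolling of participants".
- **Who knows.** The same section says: "The treatment assignments are known to the study coordinator who maintains the allocation master list in a sealed, opaque envelope". It names participants, treating clinicians and outcome assessors as blinded. The coordinator is not on that list.
- **Who checks the data.** Under Monitoring and inspection, entered data "is assessed for integrity and consistency by members of the research team in the following order: the study coordinator", then the principal investigator, then the statistical sub-investigators.
- **Masking of the product.** Placebo capsules are made to resemble the active ones as far as possible, packaging is identical, and lid undersides are swabbed with cinnamon oil in both arms.

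**The concern.** The stated safeguards (locked cabinet, sealed envelope, password, matched packaging) protect the list and the look of the product. None hides the group number printed on the bottle. This matters in two ways.

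First, blinding has a single point of failure. A shared number lets staff pool side effects by number, lets participants compare bottles, and turns any one decoded bottle into a decoded group. The documents make this plausible: the product has been on open sale since 2009, so capsules can be compared, and recruitment includes support groups, where participants may know one another.

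Second, a visible group number shows which group each earlier participant at the site joined. With a known block size, that history tells staff something about the next assignment.

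What could be affected is who is enrolled, diet and activity during follow-up, adherence (which decides per-protocol membership), reporting of adverse events and judgement of their cause.

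**Working it through.** **The plan's own figures.** The article gives no figure for predictability. Its enrolment figure sets the scale: a two-sided t test at 0.91 SD, alpha 0.05 and 80% power needs 19.96, so 20 per arm, 40 in all; 40 × 1.1 = 44 enrolled, with a ceiling of 66. Both are taken as stated.

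**Reach of one decoded bottle.** With two numbers in use, knowing one gives the other by elimination. If the same two numbers serve every site, the reach is 44 (up to 66). If numbers are site-specific, it is that site's participants. The wording favours the first reading but does not settle it.

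**Predictability of the next code.** Inputs from the article: 1:1 allocation, block of 6, by site. Assumptions: the observer has seen all earlier labels at the site, knows the block size, and guesses the code issued less often so far in the block (a coin toss if tied). There are C(6,3) = 20 equally likely blocks.

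| Position in block | Probability that the code is certain in advance | Probability of a correct guess |
|---|---|---|
| 1 | 0 | 0.5 |
| 2 | 0 | 3/5 = 0.6 |
| 3 | 0 | 0.6 × 0.5 + 0.4 × 0.75 = 0.6 |
| 4 | 2/20 = 0.1 | 0.1 × 1 + 0.9 × 2/3 = 0.7 |
| 5 | 0.4 | 0.4 × 1 + 0.6 × 0.5 = 0.7 |
| 6 | 1 | 1 |
| Sum | 1.5 | 4.1 |

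In complete blocks, 1.5/6 = 25% of codes are certain and 4.1/6 = 68.3% are guessed correctly, against 50% by chance.

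- For 44 participants: 44 × 0.25 = 11 certain; 44 × 4.1/6 = 30.1 guessed, against 22 by chance.
- For 66 participants: 16.5 certain; 45.1 guessed, against 33 by chance.

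**Incomplete blocks.** The article gives no site sizes. Assuming three sites and adding up table positions:

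- 15/15/14: certain 3.0 + 3.0 + 3.0 = 9.0; guessed 9.9 + 9.9 + 9.3 = 29.1.
- 20/14/10: certain 4.5 + 3.0 + 1.6 = 9.1; guessed 13.4 + 9.3 + 6.5 = 29.2.
- 30/8/6: certain 7.5 + 1.5 + 1.5 = 10.5; guessed 20.5 + 5.2 + 4.1 = 29.8.

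Out of 44, that is 20 to 24% certain and 66 to 68% guessed.

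**Which element drives it.** With group codes still visible, blocks of 4, 6 and 8 give 33%, 25% and 20% certain, and 71%, 68% and 67% guessed. Changing the block size therefore does little. With unique numbers the label says nothing about earlier assignments: none is certain, guesses fall to 50% (22 of 44), and a code-break exposes one person.

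**The case against.** The strongest reply is that tallying labels predicts a number, not a treatment. Until someone learns which number is active, a recruiter cannot steer people towards either arm. Directed selection needs sight of earlier labels, knowledge of the block size and a decoded label together. Entry also rests on laboratory values or physician referral, which narrows discretion. This stands. A reader might infer that allocation concealment is defeated; the documents support only that it is weakened.

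A reader might also take the batch number on the label ("primary research site name, batch number, and IRB protocol number") as a second clue to treatment. The same section says that active and placebo capsules come from the same lot, so the text gives no basis for that.

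A third reply concerns the coordinator. The article discloses that the coordinator knows the assignments, does not claim otherwise in its list of blinded parties, and does not say that the coordinator enrols participants or assesses outcomes. Serious adverse events lead to withdrawal and reporting whatever their suspected cause, which leaves little room for handling that differs by arm. So this is not a contradiction, and it does not cause the labelling problem. It remains an avoidable exposure in data review.

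Finally, all eight primary outcomes in Table 2 are laboratory values or are calculated from them. That limits measurement bias, but it does not protect behaviour, adherence, retention or adverse event reports.

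**Conclusion.** The label is a real design defect and should be changed. One decoded number exposes every participant who carries it: 44, up to 66, if two numbers serve the whole trial; one site if numbers are site-specific. The effect on concealment is partial. A fully informed observer is certain of 25% of codes and guesses 68% in complete blocks, or 20 to 24% and 66 to 68% under the assumed splits with incomplete blocks. These become predictions of treatment only after decoding. The fixed block of 6 is not itself the defect. The coordinator's place at the head of data review is a separate, secondary weakness. Nothing in the article shows that a code has been broken.

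**What to change.** **Main change.** For remaining participants, print a unique participant or kit number on each bottle, linked to arm only in the restricted list, and provide for breaking the code one participant at a time.

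**Secondary change.** Leave the list solely with the team member who already controls the sequence, so that the coordinator is blinded. Alternatively, have existing blinded staff carry out the first data review.

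**Optional.** Undisclosed, varied block sizes for future allocations are good practice but add little once labels are unique.

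**Cost.** Relabelling of the remaining stock, a link from kit numbers to the list, and an amendment with IRB approval. The list needs regenerating only if block sizes change. The article does not show whether current staffing covers the change of reviewer. Because recruitment was already active, concealment cannot be restored for those already enrolled; the report should say how many participants were enrolled under the group-level labels.

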### Randomization and blinding

Treatment assignment is randomly assigned, in a 1:1 ratio, at each site using a block size of 6. The block randomization sequence schedule is password-controlled by an appointed research team member not involved in the screening or enrolling of participants. The treatment assignments are known to the study coordinator who maintains the allocation master list in a sealed, opaque envelope. Participants, treating clinicians, and outcome assessors are blinded to intervention group status.

### Sample size

The research team aims for a final sample of 40 participants with prediabetes in this clinical trial. Participants are recruited from within clinical practices, mobile health screenings conducted as part of a separate non-intervention study [106], support groups, and health fairs, with 20 participants allocated to the active group (GlucoSupreme™ Herbal) and 20 participants allocated to the control group (placebo). In order to account for a conservative and higher-than-expected dropout rate of 10%, 44 participants will be enrolled to achieve the target sample size. The sample size of 44 participants was estimated by assuming 80% statistical power, a significance level (alpha) of 0.05 using a two-sided, two-sample, equal variance *t* test, an anticipated difference in group means of 0.91 standard deviations for continuous variables, and 10% attrition. The sizes of these treatment effects are large (i.e., between-group differences will need to be considerable in order for the treatment to demonstrate statistically significant improvements relative to placebo).

This study will utilize an adaptive sample size re-estimation (SSR) approach [107] where participant enrollment may be extended beyond the originally planned sample size if interim effect size is smaller than anticipated, but still promising, thereby preserving study power. The adaptive SSR technique will include: (1) examination of available unblinded endpoint data by the study statistician after 30 subjects are enrolled, (2) calculation of conditional power (CP), and (3) sample size modification in order to maintain study power, if required, based on pre-defined limits. CP is defined as the power of rejecting the null hypothesis at the end of the trial conditional on the observed data accumulated up to the time of the planned interim analysis. CP estimates will be categorized into one of three “zones”— Favorable, Promising, or Unfavorable. The Favorable zone will be defined as CP ≥ 80%. CPs in the Favorable zone will require no sample size adjustment (*n* = 40). Similarly, CP estimates that fall into the Unfavorable zone (CP < 50%) will require no sample size modifications (*n* = 40). However, if CP falls into the Promising zone (CP between 50 and 79%), the sample size will be recalculated such that CP equals the originally planned statistical power (i.e., 80%), up to a maximum of 66 subjects. This methodology preserves the overall type I error rate, no adjustments to alpha levels or confidence intervals are necessary, and standard statistical tests can be used for data analysis. Should the trial need to utilize adaptive SSR and enroll to the maximum sample size of 66, a difference in group means of 0.74 standard deviations could be detected.

Participants will be withdrawn from the study if they wish to withdraw or experience serious adverse events (SAEs) for any reason. If SAEs are reported, the site physician and principal investigator of the study will be contacted by the study coordinator, the participant will be withdrawn from the study, and a treatment plan will be implemented. Any dropouts will be included in the statistical analysis as intention-to-treat (ITT) using the last value carried forward (LOCF) method. Subsequent analyses will also be conducted on the per-protocol population which fully completes the study in order to determine if there are any discernible differences in these populations for the purposes of more broadly extrapolating the generalizability of results.

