
Although the study design is optimized by the selection of a study treatment containing only plant ingredients with demonstrated mechanisms of action (i.e., enzymatic, signal enhancement, etc.) [40, 43, 44, 62–92, 128], the generalizability of this study cannot be extended to smokers since they were excluded for potential safety concerns. In addition, the small sample size of this proof-of-concept and exploratory study confers a limited scope to examine potential adverse effects, and the possibility remains that investigators may find smaller than anticipated effects regarding outcomes. This may pose a potential limitation in drawing conclusions regarding outcomes. However, the study is designed to detect considerable between-group differences, determined a priori through power analyses and the accommodation of an optional use of adaptive sample size re-estimation. If the planned trial shows beneficial effects on the outcomes, subsequent trials should ideally utilize a larger sample and examine potential longer-term (> 12-week) effects of the study treatment on glycemic control.

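### The sample size re-estimation is said to preserve study power for smaller effects, but the stated zones leave overall power at about 65% at 0.74 SD

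*Protocol article*

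**What the plan says.** All of this is in the protocol article.

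- **Fixed plan (Sample size).** The target is stated as "The research team aims for a final sample of 40 participants with prediabetes in this clinical trial". Its basis is "The sample size of 44 participants was estimated by assuming 80% statistical power", with "a significance level (alpha) of 0.05 using a two-sided, two-sample, equal variance" t test and "an anticipated difference in group means of 0.91 standard deviations for continuous variables, and 10% attrition".
- **Adaptive rule (Sample size).** The rule rests on "examination of available unblinded endpoint data by the study statistician after 30 subjects are enrolled". Conditional power of at least 80% (Favorable) or below 50% (Unfavorable) leaves the size at 40. Between 50 and 79% (Promising) the size is raised until conditional power is 80%, with a ceiling of 66.
- **What is claimed for it (Sample size).** Enrollment may be extended "if interim effect size is smaller than anticipated, but still promising, thereby preserving study power". The third step of the technique likewise describes the size change as serving to maintain power. If the trial goes to 66, "a difference in group means of 0.74 standard deviations could be detected".
- **Discussion.** After conceding that effects may turn out smaller than expected, the article replies that the trial is built to detect large differences, "determined a priori through power analyses and the accommodation of an optional use of adaptive sample size re-estimation".

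**The concern.** Study power is the chance, before the trial starts, of rejecting the null hypothesis at a given true effect. Conditional power is that chance once the interim data are known. Raising conditional power to 80% in the trials that land in one interim zone does not bring study power to 80%: the trials outside that zone keep 40 participants and whatever power they had.

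The Promising zone is narrow, so most trials with a moderate true effect are never enlarged. A reader who takes the wording at face value, with 0.74 SD given beside it, would think the design is protected down to about that effect. A non-significant result would then look like stronger evidence against a moderate effect than it is.

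**Working it through.** **Inputs from the article:** two-sided alpha 0.05; 80% power; 0.91 SD; 20 per arm evaluable; 10% attrition; 1:1 allocation; look after 30 enrolled; zones below 50, 50–79 and at least 80%; ceiling 66; 0.74 SD at the ceiling.

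**Assumptions, because the article does not fix them:** one endpoint; all 30 evaluable at the look (15 per arm); conditional power computed at the observed trend; unadjusted final t test. The ceiling is tried as 30 per arm (60 evaluable) and 33 per arm (66 evaluable).

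**Step 1: the plan's own figures.** Power is the probability that a noncentral t variable with 2n − 2 degrees of freedom and noncentrality δ√(n/2) exceeds the 5% critical value.

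- n = 20 per arm, δ = 0.91: noncentrality 0.91 × √10 = 2.88, power 80.1%; effect detectable with 80% power 0.909 SD. This reproduces the plan, and 40 × 1.1 = 44.
- n = 30 per arm, δ = 0.74: noncentrality 0.74 × √15 = 2.87, power 80.5%; detectable effect 0.736 SD. This reproduces 0.74, and 60 × 1.1 = 66.
- n = 33 per arm: detectable effect 0.70 SD, power 84% at 0.74 SD. So 0.74 SD belongs to 60 evaluable, not 66.
- n = 20 per arm, δ = 0.74: power 62.6%. This is the trial without adaptation.

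**Step 2: width of the Promising zone.** With n₁ per arm at the look, interim statistic z₁ and final size n per arm,

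CP(n) = Φ{[z₁√n₁ + (z₁/√n₁)(n − n₁) − 1.96√n] / √(n − n₁)}.

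For n₁ = 15 and n = 20:

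- CP = 50% needs z₁ × (3.873 + 1.291) = 8.765, so z₁ = 1.697.
- CP = 80% needs z₁ × 5.164 = 8.765 + 0.842 × √5 = 10.647, so z₁ = 2.062.
- Multiplying by the standard error √(2/15) = 0.365 SD gives observed differences of 0.620 and 0.753 SD.

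The trial is therefore enlarged only if the observed interim difference falls in a window 0.13 SD wide, about a third of its standard error. At a true 0.74 SD:

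- Unfavorable: Φ((0.620 − 0.74)/0.365) = 37%.
- Promising: Φ((0.753 − 0.74)/0.365) − 37% = 51% − 37% = 14%.
- Favorable: 49%.

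**Step 3: overall power by simulation** (400,000 trials per setting, with a separate participant-level check of 100,000).

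| True effect | Fixed 40 | Stated rule |
|---|---|---|
| 0.60 SD | 46% | 48% |
| 0.74 SD | 62.6% | 64.7% (ceiling 60 evaluable), 64.9% (ceiling 66 evaluable) |
| 0.91 SD | 80% | 82% |

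At 0.74 SD the mean size is about 42. The maximum is reached in 5.0% of trials (ceiling 60) or 2.4% (ceiling 66).

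The participant-level run with ceiling 66 shows why the gain is small. Power inside the Promising zone rises from 65.7% to 82.4%, but only 13.8% of trials are there: 0.138 × (82.4 − 65.7) = 2.3 points. Even if every Promising trial succeeded, the gain would be 0.138 × (100 − 65.7) = 4.7 points, giving 62.5 + 4.7 = 67.2%.

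**Step 4: other readings, true effect 0.74 SD.**

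| Reading | Power | Maximum reached |
|---|---|---|
| 7–13 per arm at the look | 64.5–65.1% | 3.8–6.2% |
| Conditional power under 0.91 SD | 65–67% | about 0% |
| Base size of 44 evaluable | 69% | 5.3% |

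More generous rules than the one stated also fall short. Sending every Promising trial to the maximum gives 65%. Starting the Promising zone at 30% or 10% gives 67–68% or 71–72%.

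**The case against.** The operative rule is fully disclosed. The power phrase is tied in its own sentence to interim results that still look promising, and inside that zone the rule does lift power to about 82%. The article calls the study exploratory, says that differences must be considerable to reach significance, and warns in the Discussion that smaller effects may limit the conclusions. A condensed article also commonly leaves operating characteristics to the full protocol or analysis plan. This stands to a point: the missing simulation is not itself the fault. What remains is that the article asserts a property, preserved study power, that its own zones do not deliver, and the Discussion then leans on it.

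A reader might infer more than the document supports:

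- **That the 0.74 SD figure is an arithmetic error or a claim of 80% power for the adaptive design.** The sentence is conditional on enrolling to 66 and is correct for 60 evaluable. It needs a label, not removal.
- **That the maximum is reached in exactly 2–5% of trials.** That range holds only under the assumptions listed; across readings it is about 0–6%.
- **That the look will see far fewer than 30 outcomes.** The article speaks of available data and gives no accrual rate, so the number is unknown. Power at 0.74 SD hardly depends on it.
- **That the look should therefore wait for 30 completed week-12 visits.** At an assumed 1–2 enrolled per week, the 12-week wait adds 12–24 participants, so 42–54 would already be enrolled against 44 planned. That is not a cheap change.
- **That type I error is inflated.** For a single endpoint the simulated rate is 4.8–5.0%, which does not contradict the article.

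**Conclusion.** The point holds as a misstatement of what the adaptation achieves. At a true 0.74 SD the stated rule raises overall power by about 2 points, from 63% to 65%, which is about 15 points short of 80%. At 0.91 SD it raises power from 80% to 82%. The 65% rests on one endpoint, 15 per arm at the look and conditional power under the observed trend. The other readings of the stated zones give about 65–69%, and none comes near 80%.

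The planning figures themselves (40, 44, 0.91 SD, 0.74 SD) all reproduce. A smaller matter of labelling goes with this: 40 counts evaluable participants, while 66 appears to count enrolled ones, and the section sets the two side by side without saying so.

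**What to change.** In the Sample size section:

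1. Replace both statements about preserving or maintaining power with one saying that the rule restores conditional power to 80% only when the interim result falls in the Promising zone, subject to the maximum size.
2. Report the simulated overall power of the rule together with its assumptions: about 65% at 0.74 SD and about 82% at 0.91 SD for one endpoint, 15 per arm at the look and conditional power under the observed trend. If the team intends another reading, rerun the simulation under it and report that result.
3. Keep the 0.74 SD sentence, marked as the effect detectable with 80% power in a fixed sample of 60 evaluable, and not as the power of the adaptive design.
4. Give both sizes on one basis: 40 evaluable/44 enrolled and 60 evaluable/66 enrolled.

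The Discussion sentence that cites the re-estimation should be brought into line. This point calls for no change to the timing of the look. The cost is wording and a short simulation; the stated power becomes less favourable.

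### With blood drawn only at baseline and week 12, LOCF in the primary ITT analysis is baseline carried forward: every dropout is scored as no change, which attenuates the effect by about 10% at the planned dropout

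*Protocol article*

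**What the plan says.** All statements are in the protocol article.

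- **Missing data.** Under Sample size: "Any dropouts will be included in the statistical analysis as intention-to-treat (ITT) using the last value carried forward (LOCF) method". Analysis of datasets repeats LOCF for the ITT set, and Statistical analysis methods makes ITT the primary population.
- **Blood sampling.** Under Polyherbal dietary supplement intervention: "All participants visit their clinic site for two total visits over the 12-week study (i.e., baseline and at 12 weeks"; blood is taken at each of these visits. Arrangement for intervention describes week 6 as a telephone assessment. Measures for compliance of participants allows a call or a visit then, but no week-6 blood is described anywhere.
- **Sample size.** "The research team aims for a final sample of 40 participants with prediabetes in this clinical trial", then "In order to account for a conservative and higher-than-expected dropout rate of 10%, 44 participants will be enrolled to achieve the target sample size". The calculation uses "a significance level (alpha) of 0.05 using a two-sided, two-sample, equal variance" t test and "an anticipated difference in group means of 0.91 standard deviations for continuous variables, and 10% attrition".
- **Analysis.** Statistical analysis methods plans t tests between groups at each time point and also a mixed-model analysis of variance over the 12 weeks.
- **Other analyses.** Sample size commits to analyses of those who complete the study. Statistical analysis methods says only that per-protocol and sensitivity analyses may be done.

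**The concern.** LOCF presupposes a last on-treatment measurement. Here there is none: for anyone without week-12 blood, the value carried forward predates treatment. The rule therefore assigns exactly zero change in every continuous outcome, and the analysis treats that assignment as measured data.

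Three things are at stake.

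1. **Bias.** The estimate is wrong to the extent that dropouts would have changed. Missingness may also depend on treatment, because participants with serious adverse events are withdrawn.
2. **Planning.** The sample size treats the roughly four dropouts as lost and expects the full 0.91 SD in the other 40. The primary analysis returns those four as zero-change cases. The power statement and the primary analysis describe different data.
3. **Categorical endpoints.** A carried-forward baseline counts essentially every dropout as not progressing to diabetes. A dropout whose parameter was abnormal at baseline can never count as reverting to normal.

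**Working it through.** **Inputs from the protocol article.** Two-sided alpha 0.05, equal-variance two-sample t test, 80% power, 0.91 SD, 10% dropout, 44 enrolled for 40 analysed, 1:1 allocation. The article does not say whether the SD is that of the week-12 value or of the change, so both are computed.

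**Assumptions not in the article.** No mean change on placebo, and dropout unrelated to outcome, unless stated. Baseline and week-12 SDs are equal in the week-12 version.

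**Step 1: reproduce the plan.** With 20 per arm, the noncentrality is 0.91 × √(20/2) = 2.878 on 38 df, critical t = 2.024. Power is 80.1%. Enrolment: 40 × 1.10 = 44. (Dividing, 40/0.90 = 44.4, would round up to 45; the difference is trivial.) The stated figure is correct for completers.

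**Step 2: expected difference under LOCF.** Active-arm dropouts contribute zero instead of 0.91.

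- Random 10% dropout: 0.91 × 0.90 = 0.819 SD
- Exactly 2 of 22 per arm: 0.91 × 20/22 = 0.827 SD
- All 4 in the active arm: 0.91 × 18/22 = 0.745 SD
- All 4 on placebo: 0.91 SD, no dilution

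**Step 3: power with 22 per arm and random 10% dropout.** Mixing responders and zero-change cases adds 0.10 × 0.90 × 0.91² = 0.0745 to the active-arm variance.

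- *Change scores.* Dropouts have a change of exactly zero, so the variances are 0.90 + 0.0745 = 0.9745 (active) and 0.90 (placebo). Pooled SD = √0.937 = 0.968. Standardised difference = 0.819/0.968 = 0.846. Noncentrality = 0.846 × √11 = 2.806. Power is about 78%.
- *Week-12 values.* The variances are 1.0745 and 1. Pooled SD = 1.018. Standardised difference = 0.819/1.018 = 0.804. Noncentrality = 2.667. Power is about 74%.

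Simulation (100,000 trials per scenario, 22 per arm) agrees:

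| Dropout | Mean difference (SD) | Power, change score | Power, week-12 value |
|---|---|---|---|
| Random 5% | 0.86 | 81.1% | 79.1% |
| Random 10% | 0.82 | 78.7% | 74.3% |
| 2 active, 2 placebo | 0.83 | 79.6% | 75.3% |
| 4 active, 0 placebo | 0.74 | 69.8% | 65.0% |
| 0 active, 4 placebo | 0.91 | 87.1% | 83.6% |

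On the change scale, the four returned participants nearly offset the dilution. On raw week-12 values they do not.

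**Step 4: type I error.** With two dropouts per arm and no treatment effect it stays at or below 5%, with or without a common drift. As an assumed illustration only: with 20% dropout in one arm, none in the other, and a common 0.5 SD drift, a spurious difference of 0.20 × 0.5 = 0.10 SD appears. Simulated type I error is then 6.3% (week-12 values) to 7.6% (change scores). With 4 of 22 dropouts in one arm it is about 5.7 to 5.9% at the same drift and 7.5 to 8.0% at a 0.91 SD drift.

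**The case against.** The strongest defence is that the numbers are small and the direction is usually cautious. About four participants are affected, in a trial that calls itself proof-of-concept and exploratory. The article describes 10% dropout as higher than expected. Balanced dropout biases toward no effect and does not inflate type I error. The article also plans completer analyses, and those need complete laboratory data, so a comparison without LOCF would exist. Sample size re-estimation can raise enrolment to 66 if the interim effect is smaller than anticipated but still promising. For a participant withdrawn after a serious adverse event, zero change may be no less plausible than full benefit.

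Much of this stands, and it lowers the severity. It does not rescue the rule. A completer analysis selects on an outcome of treatment, and the article is inconsistent on whether it will be done. Enlarging the sample does not remove attenuation.

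Three stronger readings are tempting, but the document does not support them.

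- *The trial does not deliver 80% power.* The sample size is correct for completers, and on change scores the shortfall is one to two points. The 74% applies to unadjusted week-12 values. The article fixes neither which analysis is primary nor which SD is meant, so a single figure is not justified.
- *Removing LOCF would raise power to about 89%.* That figure is for baseline-adjusted ANCOVA on observed data with an assumed baseline correlation of 0.5. In a separate simulation (8,000 trials), ANCOVA gave 88.5% without LOCF and 87.0% with it. Nearly all of the gain over 74% comes from baseline adjustment.
- *The false-positive rate is inflated.* This needs both one-sided dropout and a common drift, neither of which the article anticipates.

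**Conclusion.** The concern holds, and its core is bias. The primary missing-data rule is baseline carried forward, and it treats an assumed zero change as observed. At the article's own 10% dropout, balanced between arms, the expected difference is attenuated by about 10%, from 0.91 to about 0.82 SD. Power is about 74 to 79%, depending on the analysis scale. It falls to about 65 to 70% if all four dropouts are in the active arm, and there is no loss if all are on placebo.

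These figures assume no mean change on placebo and dropouts who would have responded like completers. If dropouts would truly have stayed at baseline, the bias disappears. If dropout differs by arm and both arms drift, the bias can go either way.

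Severity: should-fix.

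**What to change.** - Delete LOCF as the primary rule under Sample size and under Analysis of datasets.
- Make the primary ITT analysis one of two options under missing at random, on all randomised participants: the mixed model already planned, fitted to unimputed data; or baseline-adjusted ANCOVA with multiple imputation.
- Add one pre-specified reference-based or delta-adjusted sensitivity analysis, because missing at random may fail for participants withdrawn after serious adverse events.
- Keep baseline carried forward, if wanted, only as a labelled sensitivity analysis.
- If LOCF stays primary, say that it carries the pre-treatment value forward, state the attenuation of about 10%, and give power as about 74 to 79% under balanced 10% dropout.

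The cost is revised wording and a little more analysis code, with no extra participants or visits. The price is reliance on missing at random, which the sensitivity analysis is there to test. The article reports that recruitment was still open at submission, so the change could be made before analysis.
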